### 2.6. Data Analysis

#### 2.6.1. Quantitative Data

The analysis of the quantitative data will be carried out using the statistical program SPSS v-21 (IBM Corp., Armonk, NY, USA) [70]. Firstly, missing data at the level of the Likert scale questionnaires will be studied. Little’s MCAR test will be used to verify whether missing data per questionnaire are below 10%, which will mean that they are randomly distributed. If this assumption is met, it will also be verified whether missing data per item have a percentage below 5% and, if so, the data will be imputed through the SEM procedure using the expectation maximization (EM) algorithm from SPSS. For those cases with missing data at the questionnaire level, the cases will be discarded [71].

The distribution of the values will also be evaluated through asymmetry and kurtosis, and the presence of extreme cases in the variables studied will be examined by analyzing the interquartile ranges through stem and leaf graphs [72].

Moreover, other statistical assumptions for the parametric tests will be checked and reported (i.e., sphericity, normality, linearity, homogeneity, and absence of multicollinearity and singularity) [73]. If the sphericity assumption is not fulfilled, the *F*-test will be adjusted as an alternative for analysis with the Greenhouse–Geisser index, reducing the degrees of freedom associated with the *F* statistic of the ANOVA as a function of the corrective factor ε [74]. If normality violation occurs, parsimony transformations will be applied to correct the non-normal distributions [75]. If multicollinearity applies, composited factors will be computed for those involved variables.

The sociodemographic variables will be used to describe the samples, to control for them in the main analyses, and to achieve equivalence between the characteristics of the control group and those of the intervention group. Both descriptive and correlational analyses will be performed as preliminary analyses.

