The effectiveness of the MBSR-P intervention will be examined by performing two-way repeated measures ANOVA for each effectiveness dimension studied, with the group (0 = *control*, 1 = *intervention*) as the factor. Interaction effects will be examined. *R*^2^ will be computed as the effect size index, and will be evaluated according to the conventional levels of 0.01, 0.06, and 0.14 for the small, medium, and large effect size levels, respectively [67]. The corrected *R*^2^ will be calculated taking into account the within- and between-subjects errors [75]. In the event that the assumptions for these analyses are not fulfilled (e.g., if normality is violated and not able to be fixed by variable transformations), Wilcoxon’s non-parametric tests will be used as an alternative [74]. Mean and standard deviation will be provided for participants’ satisfaction, and for the implementation of information registered in the field diaries.

Figure 2 shows the steps that will be followed for quantitative data analysis.

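### In the two-group pre/post analysis, the Wilcoxon fallback in its usual forms does not test the group-by-time interaction that defines effectiveness

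*Protocol article*

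**What the plan says.** The main analysis in Section 2.6.1 is a "two-way repeated measures ANOVA for each effectiveness dimension studied, with the group (0 = *control*, 1 = *intervention*) as the factor", followed by "Interaction effects will be examined". Section 2.5.3 bases the first sample size on the within-between interaction of the same ANOVA (two groups, two time points).

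The fallback comes in two steps in Section 2.6.1. First, "If normality violation occurs, parsimony transformations will be applied to correct the non-normal distributions". Then, if assumptions are still not met, for example "if normality is violated and not able to be fixed by variable transformations", Wilcoxon's "non-parametric tests will be used as an alternative". The text does not say whether this is the signed-rank or the rank-sum test, or whether it is applied to post-test scores or to change. It gives no rule for comparing change between the groups.

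Section 2.4.2 states that the groups will not be randomised. Controls come from the waiting list and are matched on the child's age category, the child's diagnostic category and the parent's sex. Baseline outcome scores are not matched. Section 2.5.2 plans pre-test and post-test questionnaires for the controls. Section 2.5.3 sets minimum sizes of 34 (intervention) and 20 (control).

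**The concern.** A fallback should answer the same question as the analysis it replaces. Here that question is whether change differs between the groups. The two textbook uses of a Wilcoxon test in a pre/post study do not answer it:

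- The signed-rank test asks whether one group changed. Run once per group, it invites comparison of two p-values, and the larger group reaches significance more easily when both change by the same amount.
- The rank-sum test at post-test asks whether the groups differ at the end. Without randomisation, an initial difference can appear as an effect or hide a real one.

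An outcome that triggered the fallback could therefore be reported from an uncontrolled or baseline-confounded comparison, alongside other outcomes judged by the interaction. Such a test would also lose the sociodemographic control that Section 2.6.1 promises for the main analyses.

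**Working it through.** **1. The plan's own figures.** Inputs from Section 2.5.3: f = 0.25, α = 0.05, correlation 0.50, sphericity 1, target power 0.80. With N participants and m time points, the noncentrality is λ = f² × N × m / (1 − ρ).

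- Interaction, N = 34, m = 2: λ = 0.0625 × 34 × 2 / 0.5 = 8.5. With 1 and 32 degrees of freedom the power is 0.807; at N = 33 it is 0.795. The stated 34 reproduces.
- One group, three time points: power 0.812 at N = 28 and 0.796 at N = 27. The stated 28 reproduces.

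The sample size calculation thus concerns the interaction. With two time points, that interaction is the t-test on change scores. At correlation 0.5 the SD of change is √(2 × (1 − 0.5)) = 1 score SD. A difference in change of 1 SD with 17 per group gives a squared noncentrality of 1 / (1/17 + 1/17) = 8.5, the same value.

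**2. The fallback when there is no group-by-time effect.** Simulation with 34 and 20 participants, correlation 0.5 (on the underlying normal scale for skewed scores), two-sided 0.05, 4,000 runs per row. The shifts, baseline differences and distributions (normal, or skewed of lognormal type) are assumptions. Entries are proportions of runs with p < 0.05.

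| Scenario | Scores | Signed-rank, intervention | Signed-rank, control | Intervention only | Rank-sum, post-test | Rank-sum, change |
|---|---|---|---|---|---|---|
| Both improve 0.25 SD | normal | 0.290 | 0.180 | 0.239 | 0.047 | 0.048 |
| Both improve 0.25 SD | skewed | 0.529 | 0.339 | 0.344 | 0.052 | 0.049 |
| Both improve 0.5 SD | normal | 0.792 | 0.537 | 0.369 | 0.048 | 0.048 |
| Both improve 0.5 SD | skewed | 0.945 | 0.763 | 0.224 | 0.044 | 0.059 |
| Baseline differs 0.3 SD, no change | normal | 0.054 | 0.054 | 0.052 | 0.177 | 0.047 |
| Baseline differs 0.3 SD, no change | skewed | 0.046 | 0.042 | 0.044 | 0.463 | 0.046 |
| Baseline differs 0.5 SD, no change | normal | 0.045 | 0.049 | 0.042 | 0.394 | 0.054 |
| Baseline differs 0.5 SD, no change | skewed | 0.046 | 0.046 | 0.044 | 0.799 | 0.050 |

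The groups are independent, so the intervention-only column can be checked by hand. At 0.5 SD, normal: 0.792 × (1 − 0.537) = 0.367. At 0.4 SD of change, signed-rank significance is 0.596 in the intervention group and 0.370 to 0.406 in controls, which gives 0.596 × 0.594 = 0.354 to 0.596 × 0.630 = 0.375. For equal changes of 0.3 to 0.5 SD of change, the pattern occurs in about 28% to 37% of normal runs and 12% to 38% of skewed runs, depending on the shape assumed. Rank-sum on change stays at 4% to 6%.

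**3. Masking.** Let the intervention group improve by 0.5 SD more than controls, with an opposite baseline difference of 0.5 SD. Rank-sum at post-test then rejects in 5.0% (normal) and 4.8% (skewed) of runs. Rank-sum on change rejects in 40.4% and 70.0%.

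**4. Power of the repair.** At a difference in change of 1 SD, rank-sum on change has power 92.8% (normal) and 99.1% (skewed). The t-test on change has 94.4% and 89.2%.

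**The case against.** The strongest reply is that the fallback is under-specified rather than wrong. A rank-sum test on change scores is also a Wilcoxon test, and with two time points it does test the interaction. A condensed article may leave the form and the variable to a fuller document; the figure showing the quantitative steps is not available here either. This stands in part: a reader might infer that no Wilcoxon test could serve, and that would be too strong. But the article states a fallback, its trigger and its place in the sequence, and never mentions change scores. Followed in its ordinary sense, the rule changes the question.

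Other stronger readings are tempting and are not supported:

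- *The plan will declare effectiveness when the intervention group is significant and the control group is not.* No such rule is written. The 12% to 38% describes what would follow if separate signed-rank tests were read that way. It is not the error rate of a prescribed procedure.
- *Outcomes are merged on the way to the Wilcoxon test.* The composite rule, "If multicollinearity applies, composited factors will be computed for those involved variables", is triggered by multicollinearity, not non-normality. The variables are not named and may be covariates, since sociodemographic variables are to be controlled for.
- *The transformation step should go.* An interaction does depend on the scale, but transforming before a parametric test is conventional and declared in advance. Removing it is a trade-off, not a correction.
- *The fallback is sure to be used for the symptom subscales.* A floor effect on a 0 to 3 score such as severe depression is plausible, but the article gives no distributions.

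**Conclusion.** The point holds for the two-group pre/post analysis. Effectiveness there is the group-by-time interaction, and the stated fallback does not test it in either usual form. This goes beyond missing detail, because a written rule applied in its ordinary sense would replace a controlled comparison by an uncontrolled or baseline-confounded one.

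The size is conditional on three things: that the fallback is triggered, which of the two forms is used, and the assumed shifts and distributions. With separate signed-rank tests the misleading pattern is common under equal improvement. With rank-sum at post-test, a baseline difference of 0.3 to 0.5 SD without any change gives 18% to 80% rejection. The direction of the problem does not depend on the exact values; the percentages do.

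The one-group, three-time-point follow-up has no group-by-time term and is outside this point. The stated sample sizes are not disputed here, and no change to the transformation or composite rules is asked for.

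**What to change.** In Section 2.6.1, replace the Wilcoxon sentence, for the two-group pre/post analysis, with a fallback that tests the between-group difference in pre-to-post change. Either of these would do:

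- a two-sample rank-sum (Mann-Whitney/Wilcoxon) test on change scores, reported with the Hodges-Lehmann shift and its 95% CI; or
- a permutation or bootstrap test of the same interaction model, which can keep the sociodemographic covariates.

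The cost is wording only: no extra data and no change in sample size. The first option has a small downside, since it drops the covariate adjustment; where that adjustment matters, the second is preferable.

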#### 2.6.2. Qualitative Data

For the management and coding of qualitative data, the qualitative analysis software NVIVO (QRS, Burlington, MA, USA) will be used [76]. With the information that the narratives of the participants will reveal, through the qualitative methodology, two types of analyses will be carried out depending on the information collected. On the one hand, an enumerative content analysis will be performed on the questionnaire of the intermediate phase of the intervention and on the follow-up questionnaire (Grbich, 2013, cit. in [77]). On the other hand, an inductive thematic analysis will be carried out without predetermined theoretical assumptions of the qualitative data from verbatim transcripts of the audio recordings from the discussion group [78]. The intermediate questionnaires will support the implementation analysis, and will feed the systematization of the intervention. The discussion groups will support the analysis of the mechanisms of change. Finally, the follow-up questionnaires will be useful for the examination of the transferability of the acquired practices to daily life.

The analyses will be conducted in parallel by two researchers with experience in qualitative methodology, along with an external supervisor. First, a code book will be built for each instrument following the recommendations of Braun and Clarke [78]: (1) to familiarize the researchers with the data, and (2) to generate initial codes. Additionally, for the thematic analysis, the recommendations of Braun and Clarke [78] corresponding to the study of the topics will be followed: (3) to search for themes; (4) to review the themes; (5) to define and name the themes; and (6) to write up the results.

Once the category systems are created, the researchers will code separately and, subsequently, meet to discuss the categories and ascertain the degree of inter-observer reliability, which will be calculated by dividing the total number of agreements in the coding of all categories by the total number of agreements and disagreements in all categories [79]. Moreover, for the enumerative content analysis, the percentages of participants that have mentioned each category in their narrative will be calculated in order to obtain comparative data on which elements of the intervention are more frequently mentioned, and the areas in which the program has a greater impact on their daily lives. For the representation of these data, comparative graphs of the percentages of participants in each category will be made, and word clouds of the most common narratives in the categories will be provided. The word clouds will be created to identify the most frequent concepts that are talked about in the focus groups, organized by the previously identified categories and in a visual manner. To do so, a selection of the 50 most frequent words will be carried out, using as an inclusion criterion the length of the word (more than 3 letters). Secondly, words with the same root (e.g., parent and parenting) will be grouped under the same concept (e.g., “parenting”). Finally, we will eliminate linking and non-content words such as “between” or “element”. For the inductive thematic analysis, the two researchers will go back and forth through the data separately so as to identify possible themes. Later on, the proposed themes will be shared, and the researchers will discuss and not only agree on a set of themes, but also identify higher order themes and subthemes, define them in depth, and select quotes that represent those themes and subthemes.

To reach an adequate sample size that will enable us to carry out this content and thematic analysis using a representative sample, we will use the data saturation criteria. Taking into consideration the parameters proposed by Hennink et al. to estimate the sample size in focus groups, we will carry out between five and six focus groups so as to achieve both code and meaning saturation [80]. Code saturation is defined as the moment when no additional codes appear in the data, and meaning saturation is defined in terms of whether the qualitative data provide further information or insight on the codes [80].

Figure 3 shows the steps that will be followed for qualitative data analysis.

## 3. Discussion

The practice of meditation and mindfulness has become widespread throughout the world due to the benefits that have been reported from it [19]. MBSR is one of the mindfulness-based interventions with the most evidence, and this study aims to expand a solid basis for the rigorous evaluation of MBSR with an added parenting component (MBSR-P) for families with children with mental health problems.

### 3.1. Expected Results

The MBSR-P program is a psychoeducational and multimodal intervention adapted from Jon-Kabat Zinn’s original MBSR [13,18], created for caregivers of children and adolescents with mental disorders. Although there is some evidence of effectiveness of the original MBSR program, this proposal seeks to optimally adjust the intervention program to the characteristics and circumstances of caregivers of children and adolescents with mental disorders. For this purpose, positive parenting contents will be incorporated throughout the intervention, two specific positive parenting sessions will be added, and the timing of the sessions and home practices will be modified. Thus, we expect the systematization of the intervention to guarantee the tailoring of the program to the specific needs and demands of this population [81]. The adaptation of the timing of the sessions and home practices take into consideration the already busy schedules of parents of children and adolescents with mental health problems [3,4]. The integration of the intervention in the mental health services considers their use of different services. We also expect to satisfy the demands of parents for both self-nourishing/self-care time and an improvement of parental competencies by incorporating positive parenting contents in a personal development psychoeducational intervention [3,4]. Moreover, with the systematization of the intervention, we also expect to maintain a high level of fidelity in the implementation of the intervention which, in turn, would guarantee the quality of the intervention, facilitating the acquisition of the intended objectives as well as their transferability to the participants’ daily lives [82].

The mixed-methods approach used in this study will help to provide different perspectives and complementary data of a different nature in order to obtain more complete information and understanding of how the program has an impact on different areas of parents’ lives, and how the learning obtained in the intervention context is integrated in the personal and family environment. It will also enable the more in-depth analysis of the implementation process and mechanisms of change, identifying strengths and weaknesses of the program [44].

Moreover, this research seeks to provide evidence of the effectiveness of the MBSR-P program in improving the quality of life of caregivers of children and adolescents with mental disorders, and alleviating negative symptoms through the practice of mindfulness [20]. Taking as a reference the existing literature, we expect changes in areas related to stress, mindfulness, emotional intelligence, general health, and the participants’ perceptions of efficacy in their parental roles [12,21,23,24]. As mentioned in the introduction, with the cross-cutting approach of self-regulation, it is expected that participation in the MBSR-P program will help parents of children with mental disorders to face the responsibility of caring for their children, identifying stressful situations, becoming aware of them, and improving their methods of dealing with them, displaying cognitive and behavioral patterns that are in line with the problem that arises [15]. In addition, with the contribution and use of tools and strategies, the intention is that once parents learn to positively face complicated day-to-day situations, the relationship between parents and children and the family environment are improved, increasing both individual and family satisfaction [7,16]. The analysis of the MBSR-P program will not be limited to its effectiveness; by examining whether the impact of the intervention is maintained in the mid-term and testing the application of the learned strategies in daily life, we will be able to prove whether the intervention has made a real difference in participants’ lives. Although there are no studies to our knowledge on the mid-term effects of MBSR interventions on parents with children with mental health issues, taking as a reference follow-up studies with other populations, we expect the changes in the evaluated dimensions to be maintained in the mid-term [5,83,84]. In relation to the practices learned during training, we expect meditation practices (e.g., body scan and breathing techniques) to be the ones more easily transferred to daily life in the mid-term, as they are less time consuming, do not require additional materials, and can be carried out in any setting [36].

Moreover, by analyzing the narratives of the parents after the intervention, we expect to gain insight about the mechanisms involved in their processes of change during the intervention. First, from the mindfulness-based intervention approach, and based on the existing theoretical and empirical evidence on mediators, we expect non-judgmental mindful attention, self-nourishing attention, awareness of their parental roles, awareness of their own negative patterns of communications and thoughts, and the reduction in reactivity to be identified as the pillar elements that have prompted the changes associated with their participation in the program [6,85,86,87]. Additionally, considering the relevance of home practices for the intervention outcomes, we expect the continuous use of the techniques and strategies learned throughout the program to be considered as an important element for the maintenance of changes during and after the intervention [88]. Second, from the experiential methodology employed in the MBSR-P program, we expect that participants will highlight the relevance of focusing on their own experiences to build up their learning by remodeling their beliefs, knowledge, and abilities [41]. Third, the group format is expected to favor social learning, and to be reported by the participants in terms of modeling, cognitive insight, emotional expression, or interpersonal learning [89].

### 3.2. Limitations

Finally, this study has some limitations that ought to be stated. First, the limits inherent to a real-context evaluation prevent the use of a randomized controlled trial design that would improve the rigorousness of the study approach [90]. The comparison of the MBSR-P program with the original MBSR to test the specific added value of the positive parenting component is another challenge that the authors hope to test in near-future research with a population with common characteristics in terms of the needs and demands that they face, such as parents of children and adolescents with other difficulties, such as physical health conditions [91,92]. Moreover, although giving voice to the participants is a valuable approach for understanding key intervention aspects involved in the process of change, direct testing of theoretical models is needed in order to fully map the mechanisms of change involved in the intervention [93]. This challenge could be addressed in future research benefiting from the results obtained in the current study. Despite said limitations, we think this study has relevant practical implications, as described below.

### 3.3. Practical Implications and Dissemination Plan

Mental health services are usually focused on direct interventions with children and adolescents, while parents and caregivers are often companions or helpers throughout. These services sometimes target the family as a whole; however, the wellbeing of parents as individuals and support in their parental roles are often overlooked. In addition, parents’ perceptions of their lives revolving predominantly around the caregiving of their child—not having personal time for leisure activities or self-care—often lead to an increase in stress levels and feelings of dissatisfaction with life in general [2].

Studies have shown the importance of the wellbeing of caregivers in order for them to be able to cope with the task of caring for children with mental health problems for both the prognosis of the child and the improvement of intrafamily relationships [12]. With this protocol, we seek to support a currently neglected sector, valuing the effort, perseverance, and dedication of the caregivers, which means highlighting the great relevance of their task, and the additional demands that these parents face. To adequately perform their parental responsibilities, caregivers need to have informal and formal support systems so that they can meet the different demands that they face and prevent negative interference with their daily lives and the childcare process [94].

Detailed manualization of intervention programs is crucial in program implementation and evaluation research. Manualization of the program is an important step towards guaranteeing the fidelity of the theoretical and methodological principles underpinning the intervention program and the implementation process, as well as its replicability and future dissemination among other practitioners [45,46,95]. The systematization of the evaluation protocol will guarantee a rigorous and multimodal evaluation process where adequate evaluation strategies are used. In addition, it will help to test and ensure the fidelity of the implementation process, while being flexible with the possibility of changes to adapt the intervention to the needs and demands of each group of parents [82]. This systematization will also help researchers to study and test the MBSR-P using similar methodological processes, enabling data comparability in order to provide further scientific evidence [45,46]. Therefore, the systematization of the evaluation process will enhance the intervention and implementation process, as well as facilitating the decision making concerning the allocation of public resources to support families of children and adolescents with mental health disorders, prioritizing evidence-based interventions [96,97,98].

The inclusion of measures that target mechanisms of change will promote further understanding of how the changes that take place during the intervention are related to the key components of the MBSR-P. These data will also help to improve the implementation process by identifying those practices and moments in the intervention that are key to reaching the program’s objectives [30,31]. Thus, these measures will help to further adapt the intervention to the characteristics and demands of the targeted population [81]. Transferability of the practices to daily life situations is another key component of the program. This part of the evaluation protocol will be crucial to identify facilitators and challenges in the application of the techniques and strategies to the daily lives of parents of children and adolescents with mental health disorders, as well as the influence of daily practices in the maintenance of changes in the short and medium term [93].

Regarding the dissemination plans, the results will be disseminated in different fields; one of them will be among professionals working with children and adolescents with mental health disorders, so that they are aware of the existence of the resource of the MBSR-P program to provide support to the parents of children and adolescents being treated in different services. For this purpose, information about the program and the results of the research will be incorporated into the internal coordination structure of the health service. In addition, brief online presentations will be made for practitioners from different fields who could also find this program helpful for their services. Moreover, this protocol and the results of the research will be disseminated in congresses that target practitioners. In the academic field, the data will be disseminated by publication in international high-impact journals in the field and making communications in relevant congresses.

